### Measures

#### Baseline

##### Patient level

Patient characteristics, including age, gender, comorbidities, smoking history, recent hospitalizations and current or recent medications, are captured via EHR chart review.

##### Provider level

Provider characteristics including age, gender, and years of practice are captured via self-report.

### Follow-up

#### Process

The process measurement battery is designed to assess the uptake of the iCPR tool by providers and to document the utilization of each part of the tool. This is a critical outcome because poor provider utilization of CDS and other EBM and quality improvement tools has been a frequent barrier to their success [9]. Measured markers of utilization (see Table 2) include rate of accepting the iCPR tool when triggered in an encounter, using the relevant iCPR risk calculator, use of the bundled order set linked to each risk calculator score, and use of each section of the bundled order set (orders, documentation, patient instructions, *et al*.). The rate of triggering of the iCPR tool from the various sections of the EHR will be measured in the intervention and control arm. The control arm is measured through 'shadow' simulation of the iCPR tool in the control patients, which allows comparison of triggering rates in the control and intervention.

**Table 2 T2:** Outcome measures

CPR	Process Outcomes	Primary Outcome	Secondary Outcomes
Pneumonia	% of eligible encounters accepting iCPR and using bundled order set	Number of antibiotics prescribed	Number of chest x-ray ordered
Strep throat	% of eligible encounters accepting iCPR and using bundled order set	Number of antibiotics prescribed	Number of rapid strep tests and throat cultures ordered

#### Outcome

The outcome measurement battery is designed to detect changes in clinical practice that are most likely to result from use of the iCPRs. The primary outcome is the difference in antibiotic prescribing frequency among patient encounters eligible for the iCPR tool among intervention compared to control providers. For example, for all patients presenting with symptoms that launch the pneumonia or strep throat tools, data will be collected from the EHR on the number of prescriptions for antibiotics written by providers randomized to the iCPR compared to usual-care arms, respectively. We will also examine the rate of chest x-ray orders and rapid strep throat test orders between intervention and control providers as a secondary outcome (see Table 2).

#### Data monitoring and quality control

All data collection is conducted via the EHR. Weekly reports are generated to track the frequency of the tool triggering, including the use of each component of the iCPR tools and the respective diagnostic triggers. Periodic chart reviews are conducted to monitor the appropriateness of tool triggering and to investigate any concerns raised by providers regarding usability or workflow disruptions. In addition, provider refresher training is conducted prior to residents coming onto each subsequent ambulatory care block in order to maintain a consistent ability to use the tool. The refresher consists of a videoclip simulation of a provider and patient interacting with tool.

### Statistical Analysis

The planned statistical analyses include comparing socio-demographic and other baseline characteristics. Patient comparisons will be conducted by stratifying the sample by randomization status and by condition (*i.e.*, pharyngitis and pneumonia). We will use the t-test, Wilcoxon test, or the chi-square test, as appropriate, to evaluate the balance between groups. The relative frequency of triggering of each iCPR in intervention and control patients, overall, and by where the triggering occurs (chief complaint, ordering, or diagnosis) will then be compared. We will calculate the proportion of intervention encounters in which each component of the iCPR tool, including the overall tool, the risk calculator, and the bundled order set, are used. This calculation will be repeated stratifying by test condition and by provider characteristics (training level, *et al*.). To test the effect of iCPR, we will use a generalized estimating equation model with clinician as the cluster variable, antibiotic prescribing as the outcome variable, and intervention group as the only explanatory variable. Given the nature of the possible relationship between patients in a cluster, we will use an exchangeable correlation structure for parameter estimation.

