#### Provider eligibility, consent, and randomization

All primary care providers within the medical practice were eligible for the study. The practice includes 149 primary care faculty, residents, and nurse practitioners divided into four units on the same floor. The study design was a randomized control trial in which the providers within the academic medical center outpatient practice were the unit of randomization. Faculty providers were randomized via random number generator to intervention or control in a 1:1 ratio. Medical residents were randomized within blocks according to their outpatient ambulatory care month (a period with substantially increased outpatient clinical activity) assignments to ensure even distribution throughout the academic calendar. However, due to changes in the resident calendar in year two of the study, any additional medical resident providers entering the system were added in a 1:1 fashion. Only providers randomized to the intervention are triggered by the EHR to use the iCPR tools. After randomization, all providers were invited to standardized educational forums for consent and training (if randomized to the intervention).

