### Power Calculation

Sample size was calculated as if individuals were independent, and then adjusted to account for the clustering of patients within physicians. Although patient outcomes are assumed to correlate somewhat within provider, the multicausal nature of clinical outcomes and the likely random nature of patient assignment to providers led us to estimate a small interclass correlation (intraclasss correlation coefficient for binomial response < 0.15). The calculation of sample size was performed with a significance level of 0.05 and 80% power. The adjusted sample size was calculated by multiplying the initial estimate of the number of patients by an inflation factor, which is a function of the interclass correlation and the number of the clusters. Final calculations estimated a need of 1,070 study subjects (535 in each disease condition) in total assuming a baseline rate of 30% antibiotic ordering in each condition and an estimated effect size of a 12% reduction in ordering in the intervention arm.

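### Patient-level balance between arms is to be tested with ordinary t, Wilcoxon and chi-square tests although providers were randomised; where a characteristic clusters by provider, the p-values are too small

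*Protocol article*

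**What the plan says.** Under Provider eligibility, consent, and randomization, the protocol article states that "the providers within the academic medical center outpatient practice were the unit of randomization". The same section gives the number of providers: "The practice includes 149 primary care faculty, residents, and nurse practitioners divided into four units on the same floor".

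Under Statistical Analysis, the baseline comparison is made at patient level: "Patient comparisons will be conducted by stratifying the sample by randomization status and by condition". The method follows at once: "We will use the t-test, Wilcoxon test, or the chi-square test, as appropriate, to evaluate the balance between groups". No allowance for provider is mentioned.

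Two other places do allow for it. The effect analysis at the end of Statistical Analysis is a GEE clustered on clinician with an exchangeable correlation. The Power Calculation inflates the sample size for patients nested within physicians, on an ICC for the binary response stated to be below 0.15.

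**The concern.** When providers are randomised, the sampling variance of a patient-level difference between arms includes variation between providers. The ordinary t-test, Wilcoxon test and chi-square test leave that component out. If patients of one provider resemble each other on the characteristic tested, the standard error is understated and the test rejects too often. The plan recognises this for the outcome and for the sample size, but not for the patient comparisons.

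Balance carries more weight here than in an individually randomised trial. Under Patient inclusion and exclusion criteria there are no patient-level criteria. A patient enters when a chief complaint, a diagnosis, or a diagnosis with an antibiotic order triggers the tool. Diagnoses and orders are entered after randomisation by providers who know their arm, so patient mix could differ by arm for reasons other than chance. A comparison of patient characteristics is one way to see this. A test with inflated error can present ordinary variation between providers as a difference in the patients captured.

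**Working it through.** **Inputs from the protocol article.** 149 providers; 535 subjects per condition (1,070 in total); 30% baseline antibiotic ordering; a 12% reduction; significance level 0.05 and 80% power; ICC for the binary response below 0.15.

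**Assumptions.** Two-sided tests (sidedness is not stated); all 149 providers contribute; ICC for patient characteristics between 0.01 and 0.15 (none is given).

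**Step 1: the plan's own figure.** Reading the 12% as absolute (30% to 18%), two-sided 0.05 and 80% power need 198 per arm, so 396 before inflation. The mean cluster size is m = 535/149 = 3.59. The design effect is DE = 1 + (m − 1) × ICC. To reach 535:

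- DE = 535/396 = 1.351
- ICC = 0.351/2.59 = 0.1355, inside the stated bound

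The 535 is therefore consistent with about 3.6 patients per provider. The match is not unique: with a continuity correction the starting number is 428, and an ICC of 0.10 gives 428 × 1.259 = 539. It still supports 3.59 as the cluster size for the next step.

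**Step 2: true error of an unadjusted balance test, per condition, equal volumes.** True error = 2 × [1 − Φ(1.96/√DE)], with DE = 1 + 2.59 × ICC.

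| Assumed ICC | DE | True error at nominal 5% |
|---|---|---|
| 0.01 | 1.026 | 5.3% |
| 0.02 | 1.052 | 5.6% |
| 0.05 | 1.130 | 6.5% |
| 0.10 | 1.259 | 8.1% |
| 0.15 | 1.389 | 9.6% |

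Equivalently, an unadjusted p-value of 0.05 corresponds to an adjusted value of about 0.096 when DE is 1.389.

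**Step 3: unequal volumes.** The practice mixes faculty, residents and nurse practitioners, and residents' outpatient activity rises in their ambulatory month, so equal volumes are unlikely. The document gives no measure of spread. With an assumed coefficient of variation of 0.65, m is replaced by 3.59 × (1 + 0.65²) = 5.11:

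- ICC 0.05: DE = 1.205, true error 7.4%
- ICC 0.15: DE = 1.616, true error 12.3%

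**Step 4: pooling conditions.** If both conditions were pooled, m = 1,070/149 = 7.18. At ICC 0.15 and equal volumes, DE = 1.927 and the true error is 15.8%. The plan compares within condition, so Steps 2 and 3 are the relevant ones.

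**The case against.** **The inflation depends on an ICC the document does not give.** This stands. The bound of 0.15 is for antibiotic prescribing, and the Power Calculation expects patients to reach providers more or less at random. If so, ICCs for age, gender or smoking may be close to zero, and at 0.01 to 0.02 the true error is only 5.3% to 5.6%. The upper rows of the table are a range, not an expectation.

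**The wording leaves the choice of method open.** This is weak. The qualifier most naturally means a choice among the three named tests by type of variable, and none of the three handles clustering in standard form.

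**Nothing depends on these p-values.** This stands for the primary analysis. The effect model has arm as its sole covariate, so no balance test selects a covariate or changes the model. The error also leans towards flagging imbalance, so it would not hide a real difference.

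**Stronger readings that the document does not support.**

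- A reader might infer that the triggering comparison ("The relative frequency of triggering of each iCPR in intervention and control patients, overall, and by where the triggering occurs") is wrong in the same way, and with much larger clusters if all clinic visits are the denominator. The document names neither a test nor a denominator for it, and an article may leave both to the full plan. No error can be attributed to it.
- A reader might infer that these balance tests are the trial's only safeguard against selective entry. They are not. Follow-up (Process) applies a shadow simulation of the tool to control patients, and Data monitoring and quality control provides for periodic chart review of whether triggering was appropriate.

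**Conclusion.** The point holds and is minor. The named tests do not match the unit of randomisation or the clustering the plan accepts elsewhere. Their p-values are too small for any patient characteristic that is positively correlated within provider.

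Per condition with equal volumes, the true error at a nominal 5% runs from about 5.3% (ICC 0.01) through 6.5% (0.05) to 9.6% (0.15), and is higher with unequal volumes. These figures rest on an assumed ICC, on 3.59 patients per provider, and on all 149 providers contributing. Fewer contributing providers would mean larger clusters and more inflation. Residents added in year two would work the other way.

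The primary GEE estimate and its error rate are not touched. What is affected is how imbalance between arms is reported and interpreted in a trial where patients enter after randomisation.

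**What to change.** In Statistical Analysis, replace the balance-test sentence for patient-level characteristics with one of two options:

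- compare arms by a method that accounts for provider, for example a GEE clustered on clinician as already planned for the outcome, with a link suited to each variable; or
- report standardised differences by arm and condition, without p-values.

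Either cures the defect; the choice is one of reporting convention. Keep the t-test, Wilcoxon and chi-square tests for provider-level characteristics (age, gender, years of practice), where the provider is the unit. If the triggering comparison is to be formally tested, state that the same clustered method applies.

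The cost is a change of wording and a few lines of analysis code. No further data are needed, because the clinician identifier is already required for the primary model.

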### Power Calculation

Sample size was calculated as if individuals were independent, and then adjusted to account for the clustering of patients within physicians. Although patient outcomes are assumed to correlate somewhat within provider, the multicausal nature of clinical outcomes and the likely random nature of patient assignment to providers led us to estimate a small interclass correlation (intraclasss correlation coefficient for binomial response < 0.15). The calculation of sample size was performed with a significance level of 0.05 and 80% power. The adjusted sample size was calculated by multiplying the initial estimate of the number of patients by an inflation factor, which is a function of the interclass correlation and the number of the clusters. Final calculations estimated a need of 1,070 study subjects (535 in each disease condition) in total assuming a baseline rate of 30% antibiotic ordering in each condition and an estimated effect size of a 12% reduction in ordering in the intervention arm.

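### The 535 per condition buys 80% power for a 12-percentage-point fall only with equal provider volumes; chance variation alone takes it to about 76–77% unless the ICC is about 0.10 or lower

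*Protocol article*

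**What the plan says.** All the planning figures are in the Power Calculation section of the protocol article. The calculation was "performed with a significance level of 0.05 and 80% power". The effect to be detected is given as "an estimated effect size of a 12% reduction in ordering in the intervention arm". The control rate is set by "assuming a baseline rate of 30% antibiotic ordering in each condition". The ICC appears only as a bound ("intraclasss correlation coefficient for binomial response < 0.15"), justified partly because "the likely random nature of patient assignment to providers led us to estimate a small interclass correlation". The independent sample size was then multiplied by a factor "which is a function of the interclass correlation and the number of the clusters", giving 535 per condition and 1,070 in all.

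The number of clusters comes from the section on provider eligibility, consent and randomization: "The practice includes 149 primary care faculty, residents, and nurse practitioners divided into four units on the same floor". Allocation is 1:1 for faculty ("Faculty providers were randomized via random number generator to intervention or control in a 1:1 ratio") and for residents who joined later. The section on patient criteria sets no quota per provider; an encounter counts when a listed complaint, diagnosis or diagnosis–order combination triggers the tool. The planned analysis is a generalized estimating equation (GEE) clustered on clinician with exchangeable correlation.

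**The concern.** Two features of the calculation affect how its 80% should be read.

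First, an inflation factor built only from the ICC and the number of clusters fixes the mean cluster size but carries no information on spread around that mean. With fewer than four eligible encounters per provider per condition, the spread is bound to be large relative to the mean, and spread costs power when outcomes are correlated within provider.

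Second, a 12% reduction from a 30% baseline can be read as relative (to 26.4%) or absolute (to 18%). The two effects differ more than threefold in size, and the sample size fits only one of them.

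At stake is the power the trial quotes, and the effect size against which its result will be judged.

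**Working it through.** **Inputs.** Alpha 0.05 (taken as two-sided; the article does not say), power 80%, control rate 30%, 149 providers, 1:1 allocation, 535 per condition, ICC below 0.15.

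**1. Independent sample size, 30% versus 18%.**
n per arm = [1.96·√(2·0.24·0.76) + 0.8416·√(0.30·0.70 + 0.18·0.82)]² / 0.12² = 197.7, or 395.3 per condition.

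**2. Reproducing 535.**
- Implied inflation: 535 / 395.3 = 1.353.
- Mean encounters per provider: 535 / 149 = 3.59.
- With equal volumes the design effect is 1 + (3.59 − 1)·ICC, so ICC = 0.353 / 2.59 = 0.136. This respects the stated bound.
- At the bound itself the design effect is 1 + 2.59·0.15 = 1.389 and power at 535 is 79.0%.

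The plan's figure is therefore reproduced for 12 percentage points and equal volumes, with nothing in reserve at that ICC.

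**3. The relative reading.** For 30% versus 26.4% the same formula gives about 2,451 per arm before clustering. At 535 per condition, power is 15% without clustering and 12% with a design effect of 1.389. The relative reading cannot have produced 535.

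**4. Unequal volumes from chance alone.** Suppose all 149 providers are equally busy and 535 encounters fall on them at random, in line with the article's own remark on patient assignment.
- CV of encounters per provider = √(148/535) = 0.53.
- Expected number of providers with none = 149·(148/149)^535, about 4.
- Design effect under exchangeable GEE = 535 / Σ[mᵢ / (1 + (mᵢ − 1)·ICC)], where mᵢ is the number of encounters of provider i, averaged over simulated allocations.

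Results for 30% versus 18%:
- ICC 0.15: design effect 1.487, power 76%; difference detectable with 80% power, 12.5 points.
- ICC 0.136: design effect 1.445, power 77%.
- ICC 0.10: design effect 1.333, power 81%.
- ICC 0.05: power 85%.

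The simpler size-weighted formula, 1 + ((1 + CV²)·3.59 − 1)·ICC, gives 75% at ICC 0.15 and reaches 80% at an ICC of 0.098. Both formulas put the break-even ICC at about 0.10.

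**5. Real differences in volume (illustration only).** The documents give no CV. Let providers' expected volumes have a CV of 0.5, 0.8 or 1.0, with chance variation on top. The CV of the actual counts is then 0.72, 0.95 or 1.12. At ICC 0.15 the design effects are 1.57, 1.69 and 1.80, and power is 74%, 71% and 68%. At ICC 0.05, power stays above 80% in all three cases.

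**The case against.** The case for leaving the text alone has several parts.

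- **There is no arithmetic slip.** This stands. With 12 points and equal volumes the figure reproduces, and the quoted description of the inflation factor is incomplete rather than false, since at fixed N the number of clusters sets the mean cluster size.
- **0.15 is a strict upper bound, not a design value.** This also stands, and it limits the point. A reader might infer that the trial is underpowered whatever the ICC. The documents do not support that: 80% holds at an ICC of about 0.10 or lower under chance variation. But the shortfall does not depend on the bound, because it also appears at 0.136, the value that 535 implies with equal volumes.
- **An article condenses.** The absence of the formula and of a CV is not itself a fault, and the full protocol might have used an ICC near 0.10 with an allowance for unequal volumes, which would also give about 535. Even so, the article as worded ties 80% power to any ICC below 0.15, and that is not so between about 0.10 and 0.15.
- **Large differences in volume are not documented.** A reader might infer from the busier ambulatory months that residents and faculty differ widely in total volume. The text describes those months but says nothing about totals per provider over the trial. The 68% to 74% range is therefore illustrative.
- **N and the number of providers may not be fixed.** The 535 is a stated need, not a cap, and residents were added in year two. If these are beyond the 149, which is not stated, power rises: 180 providers at ICC 0.15 under chance variation give about 79%.
- **The 12% resolves itself.** Largely true, since only percentage points fit 535. A reader might still infer that a null result speaks against a 12% relative reduction. The design offers no basis for that, although a reported confidence interval would also show it.

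**Conclusion.** The point holds in a limited form. The 535 per condition corresponds to 30% versus 18% with an inflation of 1.353, equivalent to an ICC of about 0.136 over 149 providers of equal volume. Equal volumes are not attainable when encounters enter by trigger. Chance variation alone lowers power by about 3 points, to about 77% at ICC 0.136 and 76% at 0.15.

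This rests on a two-sided test, 149 contributing providers with equal expected volumes, 535 encounters per condition, and the exchangeable GEE that the plan specifies. Losses beyond that need a volume CV that the documents do not give. The effect-size wording is a clarification and depends on no assumed ICC or CV. The consequence is a modest overstatement of power over part of the permitted ICC range, not a failed design.

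**What to change.** In the Power Calculation section:

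- State the effect as 12 percentage points (30% to 18%, a 40% relative reduction).
- State the working ICC instead of only a bound.
- Express the design effect in terms of the ICC, the mean number of eligible encounters per provider and the variation in the actual counts. The CV to use is that of the observed counts, which already contains chance variation; it is not comparable with the CVs of expected volume in the illustration above.
- Restate power as about 76–77% at ICC 0.136–0.15 under chance variation, with 80% at an ICC of about 0.10 or lower. Alternatively, give a detectable difference of about 12.5 points at ICC 0.15.
- Update these figures with observed provider volumes, which the EHR data behind the weekly trigger reports should supply.

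The cost is rewording and a slightly less favourable stated power. Enrolment, randomization and the analysis model do not change.
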